#### Analytic Strategy

We will use descriptive and graphical approaches to describe demographic characteristics, evaluate distributional properties, and identify outliers. The primary outcome of this study is the number or rate of HIV tests among young sexual minority men at each of the 42 FDOH-contracted CTR agencies in the 7 Florida EHE counties. The secondary outcome of this study is the mean score changes across MS domains at each of the FDOH-contracted CTR agencies. We will use generalized linear mixed models to evaluate our outcomes under the intention-to-treat analysis framework. Specifically, we will explore the use of the mixed-effects negative binomial model or the mixed-effects Poisson regression model for estimating risk ratio between the treatment and control arms for the testing data, and a mixed-effects model with a normal distribution for the MS data. Time will be included in the model as continuous exposure. Our models will evaluate the difference between the intervention and control arms, adjusting for calendar time and exposure time, which is recommended by Nickless et al [56] to reduce bias in stepped wedge cluster randomized trials. To account for correlation between multiple tests conducted within each agency and heterogeneity between agencies, we will include an agency-specific random effect term. We will also explore the inclusion of a higher order quadratic term for time for better model fit. Akaike information criteria and Bayesian information criteria will inform final model selection. We will calculate the intervention effect after 3, 6, 9, and 12 months of exposure and the time-averaged intervention effect. We will report 95% CI and corresponding *P* values for our parameter estimates. At the conclusion of the 1-year intervention period, agencies will be randomized to continuous quality improvement versus control groups to evaluate sustainment over time. The sustainment period will be 24 months for agencies that receive intervention during the first step and 6 months for agencies that receive intervention during the last step. We will again use mixed-effects regression models to evaluate the difference between continuous quality improvement versus control groups over time.

We will conduct sensitivity analysis to evaluate a per-protocol effect of the intervention on the number of HIV tests administered to young sexual minority men. We will extend our generalized linear mixed models framework to examine the presence of mediation and moderation effects in our models. Specifically, we will examine whether there is a moderating relationship between agencies using our implementation strategies (eg, TMI coaching attendance, number of TA sessions requested, prospective improvements in domains assessed by MSs) and changes in the number of HIV tests administered to young sexual minority men over time.

#### Attrition and Missing Data

The analyses will follow an intention-to-treat approach, with observations retained in the randomly allocated cluster and phase independently of participation in the experimental interventions. Highly successful tracking and retention protocols will minimize missing data. However, some data will inevitably be missing, and multiple methods will be used to evaluate assumptions and guide the analyses: (1) for a small proportion of missing data with evidence of missing at random, the data will be analyzed using the estimation procedures described above; (2) for a nontrivial amount of missing data and evidence of missing at random, multiple imputation for repeated measurements will be used to generate complete data; and (3) for a nonrandom missing data mechanism, pattern mixture models will be used to identify and control the effect of the nonrandom mechanism.

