## Results

The study was funded on August 4, 2022. A simple randomization scheme was generated using SAS (version 9.4; SAS Institute) to assign agencies to receive feedback versus no feedback during the sustainment phase on April 18, 2023. MS visits were initiated on June 1, 2023. As of June 2024, 194 MS visits have taken place at 42 sites. In addition, 4 sites from the first block and 1 site from the second block have engaged with the study. At baseline assessment, sites exhibited the lowest competencies in relationship context, counseling session, and safer sex education, and the highest competency in the privacy and confidentiality domain.

The exploration phase is projected to last from June 1, 2023, to March 31, 2024 (10 months), for block 1 and until September 30, 2025, for block 7 (28 months), with the other blocks staggered every 3 months. The preparation phase for block 1 started on April 1, 2024, and is projected to take up to 2 months for each block. The implementation phase will last for 1 year and started on June 1, 2024, for block 1 and will begin on December 1, 2025, for block 7, with other blocks staggered every 3 months. Finally, the sustainment phase will start on June 1, 2025, for block 1 and last for 2 years. For block 7, it will start on December 1, 2026, and continue for 6 months. Data collection will be completed by May 31, 2027.

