We have some preliminary evidence that garnering participation of some CTR sites may be problematic, even though we have the full support of the FDOH. In February 2023, directors of the CTR sites in the EHE jurisdictions were sent an opt out letter describing the study and giving them the opportunity to opt out of the MS visits. Although a small percent of sites opted out after the initial mailing, a few sites opted out after our follow-up calls and others did not return our calls. As a result, we have ramped-up our site engagement efforts by conducting outreach to both FDOH and county HIV and AIDS prevention coordinators to promote the study and to verify contact information for site directors. We are currently contacting sites in the first 3 blocks through an exploration engagement email, with plans to follow-up over phone if no response is received. To date, we have engaged 8 sites in exploration visits and 3 sites in preparation visits. By emphasizing our plan to share MS data and to provide site incentives (eg, continuing education units for staff that complete the full TMI training and a US $3000 incentive for each site that elects to participate and develop an implementation plan), we hope to continue to garner interest in the study as it is beneficial for the testing agencies.

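### The missing-data rule chooses the analysis by whether data are missing at random or not, a distinction that the observed data cannot make

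*Protocol article*

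**What the plan says.** The section Attrition and Missing Data opens with intention to treat, accepts that some data will be missing, and says that "multiple methods will be used to evaluate assumptions and guide the analyses". Three branches follow:

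- Branch 1, with little missing: "for a small proportion of missing data with evidence of missing at random, the data will be analyzed using the estimation procedures described above". The procedures meant are the generalized linear mixed models of the Analytic Strategy section.
- Branch 2, with more missing: "for a nontrivial amount of missing data and evidence of missing at random, multiple imputation for repeated measurements will be used to generate complete data".
- Branch 3, where missingness is judged not to be random: "pattern mixture models will be used to identify and control the effect of the nonrandom mechanism".

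The section is not limited to one outcome. The Analytic Strategy section puts both the HIV test counts and the shopper scores under the same mixed-model framework. The only sensitivity analysis that the article names is a per-protocol analysis of the test counts. It nowhere says that pattern mixture models will be run whichever branch is taken.

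**The concern.** To choose between branches 1 and 2 on one side and branch 3 on the other, the analyst must decide whether the data are missing at random. That decision turns on how missingness relates to the values that were not seen, given those that were. The observed data carry no information on this without an assumption brought in from outside. The rule thus rests on a finding that the data cannot supply, and it is applied after they are in hand.

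Branch 3 adds a second error. It expects a pattern mixture model to find the nonrandom effect and remove it. The distribution within the missing pattern is not estimable, so the model needs an identifying restriction or a chosen shift. Its output is conditional on that choice.

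At stake is which result becomes the main one. A model that assumes missing at random and a pattern mixture model with a shift can give different intervention effects from the same data, and the plan offers no valid criterion for preferring one. A reader would also not be assured of seeing both.

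**Working it through.** The plan gives no missing-data figure to reproduce. Two checks follow: whether the rule can be operated, and how much score data could fall under it.

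**1. Can the data separate the branches?** The figures here are assumed, for illustration. Quarterly test counts are Poisson, with mean 10 before crossover and an observed mean of 12 after, so the observed rate ratio is 1.20. A fraction m of post-crossover agency-quarters is missing, with mean k × 12 in the missing pattern. With k = 1 the missingness is ignorable; with k < 1 it is nonrandom.

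True rate ratio = 1.20 × [(1 − m) + m × k]

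| m | k = 1 | k = 0.8 | k = 0.5 |
|---|---|---|---|
| 5% | 1.20 | 1.188 | 1.170 |
| 15% | 1.20 | 1.164 | 1.110 |
| 29% | 1.20 | 1.130 | 1.026 |

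For example, at m = 15% and k = 0.5: 1.20 × (0.85 + 0.075) = 1.110.

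The observed-data likelihood does not contain k. At m = 15%, the contribution of an observed count of 12 is 0.85 × P(12; mean 12) = 0.09721 for all three values of k. Yet the implied probability that an agency-quarter with a count of 4 is missing is 0.15, 0.44 and 0.82 respectively. These are three different mechanisms and three different true effects with one likelihood, so no test on the observed data can choose among them.

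The values 15% and 29% lie near the agency losses that the article allows for: 6 of 42 (14.3%) if 36 remain, and 12 of 42 (28.6%) if 30 remain. They do not forecast missing counts, because counts come from health department reporting and an agency that leaves the programme may still report.

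**2. How much shopper data could be affected?** Inputs:

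- 42 sites and 2 visits per site per quarter (Overview of the implementation package).
- Visits from June 1, 2023, and "194 MS visits have taken place at 42 sites" as of June 2024 (Results).
- Scores pooled over the two visits of a quarter (Primary Implementation Outcomes).
- Assumed: four full quarters at full scheduling for every site.

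Visits:

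- Planned: 42 × 2 × 4 = 336.
- Not done: 336 − 194 = 142, and 142 / 336 = 42.3%.

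Site-quarters, the unit in which scores are analysed:

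- Total: 42 × 4 = 168.
- Fewest covered, if every covered quarter had both visits: 194 / 2 = 97, leaving 168 − 97 = 71 empty (71 / 168 = 42.3%).
- Most covered: all 168, because 194 exceeds 168, leaving 0 empty.
- If visits were missed independently (assumed): 0.423² ≈ 18%, or about 30 site-quarters, empty.

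The share of site-quarters without a score is thus anywhere from 0 to 42%.

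**The case against.** The strongest defence is that evidence need not mean a statistical test. The section EPIS Fidelity Procedures has facilitators log contacts with sites, and documented reasons for a missed visit could make missing at random more or less plausible. That is fair, but the missing-data section names no such source, and such records support a judgement about an assumption rather than a finding that selects the main method. It is also fair that branches 1 and 2 both assume missing at random, so the substantive switch is between them and branch 3. Cut-offs for a small or nontrivial amount, and numerical shift ranges, may be left to an analysis plan that is not shown; they form no part of this point. An analysis plan could not make the branching workable without replacing it.

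A reader might go further and infer that 42% of the score data are missing, that sites opting out caused it, and that the preimplementation mean is several points too high. The documents do not support this:

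- The 42% counts visits, while the analysed score needs only one visit per quarter.
- The article reports that "a few sites opted out after our follow-up calls" and that others did not return calls, but it ties no missed visit to this, and visits took place at all 42 sites. Principal Findings also describes difficulty in recruiting, scheduling and retaining shoppers, with interest varying by location. Such causes may be ignorable given county.
- A shift in a raw mean is not a shift in the effect. The agency random effect and the calendar-time adjustment absorb part of any stable difference between often- and rarely-visited sites.
- No score difference between visited and unvisited site-quarters, and no expected effect in points, is given.

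**Conclusion.** The point holds as a fault in a stated rule. The rule selects the method by a distinction that observed data cannot draw, and it credits pattern mixture models with identifying and controlling an effect that they can only explore under assumption. This follows from the wording and needs no assumption about how much is missing.

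Its practical size is open. For shopper scores, between 0 and 71 of 168 site-quarters in the first year could lack a score, assuming four full quarters of full scheduling. For test counts, the article gives no missing amount. The rate ratios above show only that effects can differ while the likelihood does not. Neither the size nor the direction of bias in the intervention effect can be derived from the document. This is a modest, inexpensive improvement, not a threat to the trial.

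**What to change.** In Attrition and Missing Data:

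1. Name one main analysis whatever any assessment of missingness shows: the likelihood-based mixed model on all available data. If correctly specified it is valid under missing at random for any amount missing, so the switch to multiple imputation is not needed.
2. Always run a delta-adjusted pattern mixture analysis as a sensitivity analysis, with shifts allowed to differ before and after crossover.
3. Delete evidence of missing at random as a selection criterion, and delete the claim that pattern mixture models identify and control the nonrandom effect. Say instead that they show how conclusions change under stated departures.

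The cost is wording and one routine sensitivity analysis. Data collection runs to May 31, 2027, so the change can be made before the final analysis.

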#### Primary Implementation Outcomes

Using the pre-established MS domains in Table 1, we will compute an overall agency score using the pooled scores from the 2 MS visits conducted each quarter. Pooled scores will be presented to reduce potential selection bias and confounding based on whether the same or a different testing provider interacted with the shoppers at either agency visit, and to account for the variability across shoppers. We will also create domain subscores using our psychometrically tested subscales for (1) LGBT visibility, (2) medical form inclusivity, (3) perceived clinic environment, (4) privacy and confidentiality, (5) relationship context, (6) RRC, (7) safer sex education, (8) PrEP information and referral, (9) perceived testing provider competency, and 10) patient–testing provider interactions. For ease of interpretability across domains, we will normalize the pooled average scores into percentiles.

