### Hiring and Training of MSs

We will hire and train 4 to 6 MSs per region (north Florida, central Florida, and south Florida) to conduct QM assessments throughout the study period. We will use both active (eg, directly approaching young sexual minority men) and passive strategies (eg, posting advertisements on social media) to identify HIV-negative young sexual minority men (aged 18-29 years) who are interested in serving as MSs. We will also promote the opportunity via advertisements on various platforms. These platforms include lesbian, gay, bisexual, and transgender (LGBT) listservs; college listservs; HIV and AIDS community-based organizations; and local coffee shops and bars. In addition, we will use social media platforms and dating apps such as Jack’d (Perry Street Software), Facebook (Meta Software), Instagram (Meta Software), LinkedIn (Microsoft), and Idealist (Free Software Foundation).

MSs will participate in a training session that will follow the procedures we used in our previous studies [11]. Specifically, MSs will receive a structured 2-hour training session on the fundamentals of HIV or STI transmission, the guidelines and protocols surrounding HIV or STI testing and PrEP eligibility, and state-specific HIV guidelines and policies. MSs will also be trained to complete the assessment tool to optimize standardized data collection across agencies.

We will underscore the importance of being well versed in their rights and procedures, and increase skills on how to respond to worst-case scenarios (eg, how to turn down any unwanted procedures), were they ever to occur. MSs will be instructed to be honest about their sexual behaviors during their visits. For an HIV-positive test result, MSs will alert the study staff who will provide referrals for care, if needed.

MSs will be randomly assigned to each study site to avoid selection bias. The team will create a calendar for MSs to know their schedule of clinic visits. MSs will be instructed to report that they do not have income or health insurance and do not possess any proof of identification. By doing so, we will ascertain whether these are potential barriers to testing at a given location and document the lowest possible fees that may be charged to a young sexual minority man.

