### YACHT Implementation Package Specification

#### Overview

During the exploration phase, we will present at state-wide meetings and conferences to inform agencies state-wide about the initiative in collaboration with FDOH. Every quarter, each study site will receive 2 MS visits. We will use time-space sampling to ensure that varying days (weekdays vs weekends, when applicable) and times (eg, morning vs afternoon or evening) are selected for visits, thereby maximizing the chance of meeting different counselors at each agency. The exploration phase will end with virtual meetings of individual agencies with regional facilitators to orient HIV-testing directors to the program, address any initial concerns, and increase engagement with the planned implementation strategies. These meetings will aim to create an engaging, interactive environment to probe knowledge and utility of MSs for HIV-testing programs. Regional facilitators will describe the MS assessment and approaches using TMI and TA, ending the session with an overview of the study and scheduling an in-person visit for the preparation phase.

The preparation phase will occur 2 months before the implementation phase and will consist of an in-person meeting with the executive director and the leads of testing and prevention services. We will provide personalized feedback using the MS assessment findings that address environmental and interpersonal factors. We will elicit their views regarding the findings, focusing on the aspects they would like to improve. We will also suggest strategies for change and assist them with planning an intervention appropriate for their agency. To address environmental factors, we will lead agency directors in a problem-solving exercise to brainstorm ideas and develop a plan to address the components they select. To address the interpersonal factors, we will discuss how TMI may be used to improve testing provider–client interactions and discuss challenges and opportunities for improving CTR services. In collaboration with the agency, we will compile a list of staff to engage in the intervention. Consequently, the YACHT program will be adapted to each agency’s needs and culture.

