### Limitations, Foreseeable Challenges, and Potential Solutions

Staff turnover is a threat to any health force training. All trainings will be recorded so that the recorded trainings along with our TMI video examples will allow new testing providers to join the program even if they miss the original workshop. In addition, TMI webinar trainings will be offered on a rolling basis for all agencies. In addition, each agency’s implementation plan will be clearly documented and we will ensure they have a copy they can refer to and share with new staff. Another potential challenge is that agencies may close or lose funding and drop out of the study. We have included all 42 eligible agencies to reduce bias, but power calculations suggest that the study may be completed with as few as 30 agencies. In addition, the political context in Florida is currently challenging for HIV-testing sites that target young sexual minority men because images and language that explicitly support LGBT youth are banned. As a result, the evaluation and discussion of developmental and cultural aspects of CTR for young sexual minority men must be tailored to be both acceptable and clear, without penalizing sites for political factors they cannot control. Finally, MSs are likely to turn over, but we have budgeted for additional outreach and training time for new shoppers.

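### Averaging the two quarterly visits only reduces shopper variability; a visit-level model with a shopper random effect would account for it

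*Protocol article*

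**What the plan says.** - **Score.** Under Primary Implementation Outcomes: "we will compute an overall agency score using the pooled scores from the 2 MS visits conducted each quarter". Two reasons are given. One concerns whether the two visits met the same testing provider; the other is "and to account for the variability across shoppers".
- **Visits.** The Overview of the implementation package plans: "Every quarter, each study site will receive 2 MS visits".
- **Model.** Analytic Strategy specifies "a mixed-effects model with a normal distribution for the MS data". It enters time as continuous, with a quadratic term to be explored, and names an agency-specific random effect. Quantitative Measures and Data Analysis adds a possible county effect. No shopper term is named anywhere.
- **Shoppers.** Hiring and Training of MSs: "We will hire and train 4 to 6 MSs per region", in three regions, with random assignment to sites. The limitations section expects that "MSs are likely to turn over".
- **Progress.** Results, as of June 2024: "194 MS visits have taken place at 42 sites".

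**The concern.** With 12 to 18 shoppers covering 42 sites, each shopper rates several sites per quarter. A strict or lenient shopper moves all those scores together. Averaging two visits dilutes this but does not separate it from the state of the agency, and an agency random effect cannot absorb it because the shared component runs across agencies. When shoppers leave and are replaced, the shared component also changes with calendar time, which a smooth time term follows poorly.

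Two things are at stake for the implementation effect: noise that the collected data could remove, and a standard error that may be too small. Pooling also hides whether a score rests on one visit or two.

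**Working it through.** The article states no variance, standard error or power for the mystery shopper score, so there is no figure to reproduce. The variances below are assumptions.

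**1. What averaging does.** Let shopper variance be S and remaining visit variance E.
- Two different shoppers: variance of the mean = S/2 + E/2.
- One shopper twice: S + E/2.
- Two sites that share a shopper keep a positive covariance in both cases.

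Planned load: 42 × 2 = 84 visits per quarter, or 84/18 = 4.7 to 84/12 = 7 per shopper, so sharing is unavoidable.

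**2. Visits achieved.** June 2023 to May 2024 is four quarters: 42 × 2 × 4 = 336 planned. 194/336 = 58%, and 194/168 = 1.15 visits per site-quarter against 2 planned. How the missing visits are spread is not reported. Three patterns fit the same total:

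| Pattern | Two visits | One | None |
|---|---|---|---|
| Independent visits | 33% | 49% | 18% |
| Spread evenly | 15% | 85% | 0% |
| Clustered by site-quarter | 58% | 0% | 42% |

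**3. Precision.** Exact generalized least squares variances were calculated for the documented design: 42 sites, 7 steps, 5 shoppers per region, and two different shoppers per site-quarter drawn at random. Total variance was 1, site variance 0.30 and site-quarter variance 0 to 0.20. The shopper share of the remaining visit variance was varied, and time was continuous. Method A is the site-quarter mean with an agency effect (true standard error by sandwich). Method B is the visit-level model with agency, site-quarter and crossed shopper random effects.

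| Scenario | Share | SE, A | SE, B | Reduction |
|---|---|---|---|---|
| All visits, no turnover, no sustainment data* | 5% | 0.1116 / 0.0988 | 0.1107 / 0.0973 | 0.8% / 1.6% |
| same* | 10% | 0.1114 / 0.0985 | 0.1092 / 0.0949 | 2.0% / 3.7% |
| same* | 30% | 0.1106 / 0.0972 | 0.1029 / 0.0841 | 7.0% / 13.4% |
| All visits, yearly turnover, sustainment data in | 10% | 0.0959 | 0.0898 | 6.4% |
| same | 30% | 0.1066 | 0.0823 | 22.8% |
| 58% of visits, yearly turnover, sustainment data in | 0% | 0.1237 | 0.1187 | 4.0% |
| same | 10% | 0.1271 | 0.1176 | 7.5% |
| same | 30% | 0.1331 | 0.1062 | 20.2% |

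*Site-quarter variance 0.20 / 0; the other rows use 0.05.

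With all visits done and a zero share there is no gain. The 4.0% at zero share and 58% completion comes only from weighting one-visit and two-visit quarters correctly.

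**4. Test size.** The actual size of a nominal 5% test is 2 × [1 − Φ(1.96 × model SE / true SE)]. With yearly turnover, all visits and sustainment data, the agency-only model reports 0.0903.
- Share 10%: 1.96 × 0.0903/0.0959 = 1.846, size 6.5%.
- Share 30%: 1.96 × 0.0903/0.1066 = 1.660, size 9.7%.

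Over further runs with linear or quadratic time plus turnover the size was about 6-11%. With quarterly time effects it was about 4-6%. Without turnover the model standard error is about right or slightly conservative (0.0992 against a true 0.0972 at share 30%).

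**5. Where the gain comes from.** At share 30% with yearly turnover and all visits, the standard error is 0.1066 for plain means, 0.0837 for means with shopper covariance modelled, and 0.0823 at visit level. Modelling the shopper gives (0.1066 − 0.0837)/(0.1066 − 0.0823) = 94% of the gain.

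**6. Random or fixed.** Shopper fixed effects can lose precision. At share 5% with half-yearly turnover and all visits, they give 0.1005 against 0.0933 for averaging.

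**The case against.** - **Missing detail.** The article does not list every random effect for the shopper data. The agency term is justified in terms of HIV tests, and a shopper term may stand in an analysis plan that is not shown. That is fair, and silence alone would be no finding. But the article fixes a pooled score and gives a reason for it, and the shopper part of that reason is wrong as stated.
- **Invented variance.** The size rests on a shopper variance that the documents do not give. The instrument is described as psychometrically sound and shoppers are trained for standardized collection, so a low share is plausible, and the gain is then small. This stands. A reader might infer that a visit-level model is always clearly more precise; the documents do not support that.
- **Bias.** A reader might infer that shopper differences confound the intervention effect, or that the article claims pooling removes confounding by shopper. Neither is supported. Shoppers are randomly assigned to sites, and the confounding clause concerns testing providers.
- **Averaging is not the main cause.** Step 5 confirms this: the missing shopper term matters far more than the averaging.
- **Form of time.** The inflated test size needs both turnover and a continuous time term. That is true, but the article plans the one and expects the other.
- **Estimation cost.** The calculations treat variance components as known. Site-quarter variance is identified from two-visit quarters, and shopper variance from 12 to 18 people at a time, so part of the gain may be lost in practice.

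**Conclusion.** The point holds in a conditional form. Pooling two visits reduces shopper variability without accounting for it, and the named agency effect leaves the correlation between sites sharing a shopper unmodelled. The consequence is lost precision and possibly standard errors that are too small, not systematic bias.

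The reduction in standard error from modelling shoppers at visit level ranges from near nil (share 10% or less, all visits done, no turnover) to roughly 20-25% (share 30%, yearly turnover). With continuous time and turnover, a nominal 5% test can run at about 6-11%. The visit-level random-effects model was not less precise in any scenario calculated. The weighting loss from incomplete visits depends on how they are spread: the calculation puts it at about 4% if visits go missing independently, and it would disappear if they were missing in pairs.

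All sizes rest on assumed variances treated as known, few replicate assignments per scenario (about one percentage point of noise), and, in the 58% rows, on first-year completion continuing.

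**What to change.** - Analyse each visit's score in a normal mixed model with crossed random effects for agency and shopper, plus an agency-by-quarter random effect. Use random, not fixed, shopper effects.
- Report the estimated shopper variance, so that readers can see how much it mattered.
- Keep pooled scores for the site feedback reports.
- Reword only the shopper clause under Primary Implementation Outcomes, to say that pooling reduces variability across shoppers. The clause on testing providers can stay.

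Cost: no new visits or instrument. The analysis file must keep shopper and visit identifiers, and the model has additional variance components to estimate. Data collection runs to May 31, 2027, so the change can still be prespecified.
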